#### 4.7.3 Childrens' clinical outcomes

Proportion of children who undergo cranial CT: The study coordinator enrolling the parent(s) will ascertain this in real time and confirm the data by health record review of the child of the enrolled parent(s).

Healthcare utilization: We will assess healthcare utilization for the subsequent 7-days after the ED visit. Healthcare utilization will include measures such as hospitalization, re-hospitalization, primary and specialty visits, and diagnostics including CT use which will be obtained via a health record review, review of itemized hospital charges on the UB-92 and UB-04 forms (summary billing statements), and parental report via the 7 day follow-up by the study coordinator. The parent self-report will capture any ED readmissions, outpatient and subspecialty visits, the number of each type of outpatient visit, imaging data, procedures, and inpatient hospitalizations (including admission and discharge dates, reason for admission, neurosurgical procedures, and discharge destination). To assist parents in collecting utilization data, we will provide a form to document this information at discharge from the ED or the hospital. This will allow for a more standardized collection of these data if parents receive care at a location other than the primary institution. We will also identify patients who receive a significant portion of their health care at the participating centers. For these patients, we will compare the patient reported utilization to the data from each institution's electronic medical record and administrative billing data, where available and feasible.

Safety: We will assess safety by comparing the rate of clinically-important TBI in each arm of the study. We will define clinically-important TBI as we did in our prior study: death from TBI, intubation for more than 24 hours for TBI, neurosurgical procedure, or hospital admission of 2 nights or more associated with TBI on CT. We defined this outcome to exclude brief intubations for imaging or overnight admission for minor CT

findings. We sought a meaningful measure for clinical decision-making which also accounted for the imperfect specificity of CT (i.e., false positive scans that might result in overnight admissions). Site investigators, blinded to ED data, will verify outcomes by medical record review. CT scans will be obtained at the ED clinician's discretion with helical CT scanners and interpreted by site faculty radiologists. A faculty radiologist, unaware of clinical data, will make definitive interpretations of inconclusive CT scans. Study coordinators will contact parents of children with minor head trauma starting at 7 days to ensure that no outcomes are missed. Medical records and imaging results will be obtained if a missed TBI is suggested at follow-up. If a ciTBI is identified, the patient's outcome will be classified accordingly. If we are unable to contact the patient's guardian by telephone or any secondary means of contact provided at the time of consent, we will review the medical record, emergency department/trauma process improvement records, and county morgue records, to ensure that no discharged patient is subsequently diagnosed with a ciTBI.

#### 4.7.4 Clinician reported outcomes

**Satisfaction:** We will assess clinicians' satisfaction by asking questions regarding the helpfulness and satisfaction with the way information was shared during the encounter using a 7-point Likert scale.

**Preference:** Clinicians will identify their preference in decision-making style after the encounter with each enrolled parent(s) (Control preference scale). This scale contains 5 levels which will be reported as frequencies and counts along with correlation to the patients reported control preference scale.

### 4.8 Statistical Analysis

#### 4.8.1 Analysis Plan

We will conduct the study according to the intention to treat principle, including all parent-children dyads in the arm to which they were randomized, regardless of whether they received the intervention assigned. We will adhere to the CONSORT guidelines to transparently report study results and ensure that sufficient information is included to allow for assessment of the study's internal and external validity.

We will compare outcomes between study arms using t-tests for continuous outcomes and  $\chi^2$  tests for dichotomous outcomes, adjusted for clustering by clinician and stratified by study site. If there are differences in baseline characteristics between the two study groups, these will be accounted for using hierarchical generalized logistic or linear regression models that include an indicator for study arm^28.

We will perform descriptive analyses to describe any potential heterogeneity of treatment effect (HTE) and facilitate synthesis of subgroup results in future meta-analyses. We will conduct descriptive HTE analyses by age, gender, parent race/ethnicity, GCS score, and level of parental education (collected in post-visit surveys). The outcomes assessed with HTE analyses will be the same as those assessed in the trial (e.g., patient-centered outcomes such as parental knowledge, engagement,

satisfaction and healthcare utilization). We will also conduct interaction testing to determine the interaction between the decision aid and each pre-specified patient characteristic.

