## 1.0 Specific Aims

Our long-term goal is to promote evidence-based, patient-centered evaluation in the acute setting to more closely tailor testing to disease risk. As PCORI specifies, to “compare the use of risk stratification tools with usual clinical approaches to treatment selection or administration,” we propose the following Aim:

- Test if the decision aid, Head CT Choice, improves validated patient-centered outcome measures and safely decreases healthcare utilization.

Hypothesis: The intervention will significantly increase parents’ knowledge, engagement, and satisfaction, decrease the rate of head CT use, and decrease 7-day total healthcare utilization with no significant increase in adverse events.

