#### 4.8.3 Sample Size Estimation

Patient knowledge will be the primary outcome, as it was considered to be the most important endpoint by our patient representatives on the ED Patient Advisory Council. In order for the study findings to maximally impact practice and policy, however, we will need to be adequately powered to detect differences in the outcomes of interest to each of the stakeholders.

Accounting for a lost to follow-up rate of as high as 5% (there was 2% lost to follow-up in our pilot trial), approximately 75 clinicians (assuming an average of 15 clinicians/site) will enroll 950 patients. This will provide the following power to detect differences in each of the patient and stakeholder-important outcomes (using a 2-sided hypothesis test and an alpha of 0.05):

| Outcome (n = 950)                                                                                | Usual Care* | Decision Aid* | Difference | Power |
|--------------------------------------------------------------------------------------------------|-------------|---------------|------------|-------|
| Parent knowledge                                                                          | 44%         | 60%           | 16%        | >99%  |
| Parent engagement in the decision making process                                          | 7.0 (5.5)   | 27.0 (8.2)    | 20.0       | >99%  |
| Decisional conflict †                                                                     | 36 (19)     | 21 (21)       | 15         | >99%  |
| Trust in the physician                                                                    | 79 (20.0)   | 84 (20.0)     | 4.1        | 86%   |
| Parent satisfaction with the decision made (% agree or strongly agree they are satisfied) | 70.0 (26)   | 80 (26.0)     | 10.0       | >99%  |
| Safety (clinically-important traumatic brain injury) ‡                                    | 0.9%        | 0.9%          | 0%         | 82.5% |
| Proportion of children who undergo head CT §                                              | 49%         | 34%           | 15%        | 95%   |
| Healthcare utilization                                                                    | 8.3 (0.8)   | 6.8 (0.7)     | 1.5        | >99%  |

\*Estimates were determined from our completed randomized trial.

†Lower decision conflict scores indicate less conflict experienced by patients related to feeling uninformed.  

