‡ Noninferiority, 1-sided test with alpha = 0.05 with a maximum difference of 2%. Baseline rates determined from the PECARN prediction rule study.  
§ Obtained from the rate of CT in the moderate risk group of patients in the PECARN prediction rule study.

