#### 4.8.4 Allocation process

Clinicians will be randomized at the beginning of the study and, if necessary, when first treating an eligible patient. Clinician randomization will be stratified by study site and according to whether they are pediatric emergency clinicians or not. To maintain balance the randomization algorithm utilized will balance across the stratification factors dynamically as clinicians are enrolled.

Randomization will be assigned on a 1:1 basis across arms. Though we will not be able to blind parents and clinicians to use of the decision aid, we will blind the investigators and all nonclinical stakeholders to study arm.

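### Safety is powered as a noninferiority test with a 2-point margin, but the analysis plan and the hypothesis describe a difference test

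*Protocol*

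**What the plan says.** Four places in the protocol bear on how safety is judged.

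- **1.0 Specific Aims.** The hypothesis is that the decision aid improves the other outcomes "with no significant increase in adverse events". No margin is given.
- **4.7.3 Childrens' clinical outcomes.** "We will assess safety by comparing the rate of clinically-important TBI in each arm of the study". The composite is defined there, but no margin or confidence-limit rule.
- **4.8.1 Analysis Plan.** Continuous outcomes get t-tests. Binary outcomes get chi-square "tests for dichotomous outcomes, adjusted for clustering by clinician and stratified by study site". Safety is not set apart.
- **4.8.3 Sample Size Estimation.** The table's general basis is "using a 2-sided hypothesis test and an alpha of 0.05". The safety row (0.9% in both arms, difference 0%, power 82.5%) carries a footnote: "Noninferiority, 1-sided test with alpha = 0.05 with a maximum difference of 2" per cent.

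The margin therefore appears only in a footnote to the power table.

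**The concern.** A noninferiority test and a difference test have opposite null hypotheses. Under noninferiority, harm of at least 2 points is presumed until the data exclude it, so sparse data make the claim harder. Under a chi-square test read as no significant increase, equality is presumed, so sparse data make a reassuring result easier to obtain. With a rare outcome and clinicians as the unit of randomization, information on ciTBI is limited and the two rules can disagree often.

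The aim in 1.0 is to reduce utilization safely, so this comparison carries part of the main message. An analyst who followed 4.8.1 and 1.0 literally would not run the test that the sample size was built for.

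**Working it through.** **Inputs**

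- Usual-care ciTBI rate 0.9%, margin 2 points, one-sided alpha 0.05, stated power 82.5% (4.8.3 table and footnote).
- Size: "approximately 75 clinicians (assuming an average of 15 clinicians/site) will enroll 950 patients", or 950/75 = 12.67 per clinician.
- Allocation: "Randomization will be assigned on a 1:1 basis across arms" (4.8.4), taken as 475 children per arm. Clinicians are the randomized unit, so this is an approximation.
- Loss: "Accounting for a lost to follow-up rate of as high as 5" per cent. If this comes off the 950, about 451 per arm remain.
- Intracluster correlation (ICC): not stated. Design effects from 1 to 1.6 are assumed, applied by dividing n by the design effect.

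**1. The plan's own figure (82.5%)**

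Normal approximation, n = 475 per arm:

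- Variance at 0.9%/0.9%: SE = √(2 × 0.009 × 0.991 / 475) = 0.00613. Power = Φ(0.02/0.00613 − 1.645) = Φ(1.62) = 94.7%.
- Null variance at the margin (0.9% and 2.9%): SE₀ = √((0.009 × 0.991 + 0.029 × 0.971)/475) = 0.00884. Power = Φ((0.02 − 1.645 × 0.00884)/0.00613) = Φ(0.89) = 81.4%.
- First variant with an assumed ICC of 0.05: design effect 1 + (12.67 − 1) × 0.05 = 1.58, SE = 0.00613 × √1.58 = 0.00771, power = Φ(0.02/0.00771 − 1.645) = Φ(0.95) = 82.9%.

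The last two lie close to 82.5%. The figure fits a noninferiority design, and with equal assumed rates it has no meaning as power for a difference test.

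**2. Expected events**

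0.009 × 475 = 4.3 per arm at the planning rate; 0.029 × 475 = 13.8 in an arm at the margin.

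**3. The two rules at the margin (true rates 0.9% and 2.9%)**

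Chi-square, two-sided 5%, by approximation: the pooled rate is 1.9% and SE = √(2 × 0.019 × 0.981/475) = 0.00886. Power to show harm = Φ((0.02 − 1.96 × 0.00886)/0.00884) = Φ(0.30) = 61.7%, so 38% of trials show no significant increase. The table gives exact binomial enumeration; the noninferiority column uses a one-sided 95% Wald upper limit below 2 points.

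| Per arm | Chi-square: no significant increase | Noninferiority passes |
|---|---|---|
| 475 | 37% | 7% |
| 451 | 39% | 7% |
| 475 with design effect 1.6 (effective 297) | 56% | 7% |

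At 475 per arm without clustering, a Farrington-Manning score test passes in 5%. A one-sided 5% chi-square, which the protocol does not state, would miss the increase in 25%.

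**4. One possible result**

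Four events against 11, with 475 per arm: the difference is 7/475 = 1.47 points. Chi-square gives p = 0.068, no significant increase. The Wald SE is 0.81 points, so the one-sided 95% upper limit is 1.47 + 1.645 × 0.81 = 2.8 points, and noninferiority is not shown. The same data give opposite messages under the two rules.

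**The case against.** The strongest reply is that the noninferiority test is already in the protocol. The footnote fixes type, sidedness, alpha and margin for this one outcome, and a specific statement would normally govern a general sentence. The hypothesis in 1.0 is an expectation rather than a decision rule, and it speaks of adverse events, not ciTBI. The interval method could sit in a separate analysis plan.

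Much of this stands. It shows what the sponsor probably intends, and it lowers the severity. It does not remove the conflict: 4.8.1 is where the analysis is specified, it names a test for binary outcomes without an exception, and nothing there points to the footnote.

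Several stronger readings are tempting but not supported:

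- *That the trial will declare safety from a non-significant chi-square.* No section says so. The wording permits it.
- *That a tripled rate breaches the margin.* 0.9% to 2.7% is 1.8 points, inside the margin. The fault lies in the decision rule, so the 2.9% case is the relevant one.
- *That 82.5% is wrong, or that it reveals an ICC of 0.05.* It is approximated with clustering (82.9%) and without (81.4%), so no ICC can be recovered from it.
- *That fewer CTs in the decision-aid arm will hide ciTBI.* One component of the composite requires TBI on CT, but the protocol gives no basis for sizing any bias. Section 4.7.3 partly meets the point with parent contact from 7 days and record review, and late-found cases are classified as ciTBI.
- *That most ciTBI is settled by the injury before the discussion.* The protocol contains no figure for this.

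**Conclusion.** The contradiction is real and wrong as written: the powered test, the stated test and the hypothesis do not describe the same safety question. When the true excess equals the protocol's own limit, the difference test gives no significant increase in about 37% of trials, against about 7% passing noninferiority.

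The 37% assumes 475 evaluable children per arm, a two-sided 5% chi-square and no clustering. The 56% rests on an assumed design effect of 1.6 and should be quoted only as such. The noninferiority pass rate at the margin is about 5% to 7%, depending on method.

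This should be fixed, but it is not critical: parent knowledge is the primary outcome, and the margin, alpha and direction are already prespecified.

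**What to change.** - **4.8.1:** except ciTBI from the chi-square rule. Estimate the risk difference (decision aid minus usual care) with a one-sided 95% upper confidence limit, by a method suited to sparse events and allowing for clustering by clinician. Claim noninferiority only if that limit is below the 2 points already in the 4.8.3 footnote.
- **1.0:** restate the safety part of the hypothesis as noninferiority on ciTBI under this rule, in place of the absence of a significant increase.
- **Optional:** list by arm the ciTBI first diagnosed after ED discharge, from follow-up already planned in 4.7.3. It would be rare and only descriptive, and is not part of the error.

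The cost is a wording amendment, with no added patients or data. The downside for the sponsor is that safety can no longer be claimed from a non-significant test.

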## 4.6 Calendar of Events

| Parent Forms/Schedule             | Prior to Study Enrollment | Prior to discussion  | Discussion | After discussion  | 7 Day Follow-Up |
|-----------------------------------|---------------------------|----------------------------------|------------|-------------------------------|-----------------|
| Approached            | X                         |                                  |            |                               |                 |
| Informed Consent                  | X                         |                                  |            |                               |                 |
| Pre-Encounter Survey  |                           | X                                |            |                               |                 |
| Post-Encounter Survey             |                           |                                  |            | X                             |                 |
| Phone Survey                      |                           |                                  |            |                               | X               |
| EMR Review                        |                           |                                  |            |                               | X               |

1- Discussion is the encounter between the clinician and the parent where the child's risk and parents' options for screening are discussed.

2- When consent is provided by both the parent and clinician the encounters will be video and/ or audio recorded.

3- Parents enrolled will be captured in the remote data capture system. Parents found to be ineligible or who declined participation will be assigned a generic study ID by the study coordinator and the reason for ineligibility or that the parent(s) declined will be captured in a tracking log.

4- The pre-encounter survey may be administered after the discussion, if the flow of care for the enrolled parents' child does not allow for it to occur prior to the discussion of interest. These events will be captured in the remote data capture system.

| Clinicians Forms/schedule | Prior to Enrollment of Eligible Parents | Randomization | After discussion with each enrolled parent |
|---------------------------|-----------------------------------------|---------------|--------------------------------------------|

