#### 4.8.2 Missing data

We will make every effort to minimize missing data. Trial enrollment and the fidelity of follow-up procedures will be reviewed during monthly conference calls. In our pilot trial of the Chest Pain Choice decision aid only 2% of patients were unable to be contacted by phone at 30 days for follow-up, indicating that study data were 98% complete. A study biostatistician will conduct frequency reports to assess for missing data, and the study team, which is experienced in conducting multicenter trials, will trouble shoot any problems encountered. Patients with missing outcome data will not be included in the assessment of that outcome. We will report rates of missing data for each outcome by study arm and known reasons for missing data. For data elements that are used to adjust study comparisons we will use multiple imputation to account for any that are missing at random (MAR).

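### Covariate adjustment depends on observed baseline imbalance and the clinician-type stratifier is left out of the comparison, at some cost in precision and clarity but not in validity

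*Protocol*

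**What the plan says.** Protocol 4.8.1 compares outcomes by t-test or chi-square test, "adjusted for clustering by clinician and stratified by study site". The next sentence reads "If there are differences in baseline characteristics between the two study groups, these will be accounted for", and this is to be done "using hierarchical generalized logistic or linear regression models that include an indicator for study arm". The section gives no threshold or test for a difference and no covariate list. It does not state whether the clustered test or the regression is the main result once the condition is met.

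Protocol 4.8.2 confirms that adjustment is a planned path, again without naming variables: "For data elements that are used to adjust study comparisons we will use multiple imputation".

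Protocol 4.8.4 sets out the allocation: "Clinician randomization will be stratified by study site and according to whether they are pediatric emergency clinicians or not", and "the randomization algorithm utilized will balance across the stratification factors dynamically as clinicians are enrolled". So two factors are balanced, and only one of them (site) appears in the comparison. The utilization models in 4.8.5 give insurance type and severity of illness as example covariates, not clinician type.

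On the timing of candidate covariates, footnote 4 of the Calendar of Events (4.6) says "The pre-encounter survey may be administered after the discussion" when the flow of care requires it, and that such cases are recorded. Section 4.7.1 places parent education at enrollment; 4.8.1 places it in post-visit surveys.

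**The concern.** Two features of a stated rule are at issue.

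First, covariates enter because the arms happen to differ on them, not because they predict the outcome. Parent education, health literacy, numeracy and child age are all collected or known and could plausibly predict knowledge or CT use. Under this rule they help only when chance or recruitment makes them unequal. Since the main result is not named, a reader of the final report could not tell which analysis was meant to carry the conclusion.

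Second, balancing on a prognostic factor removes its contribution from the real variability of the treatment contrast. An analysis that ignores the factor still counts that contribution as noise, so it reports a standard error larger than the true one. The trigger cannot be relied on to bring clinician type back in, because the allocation is designed to keep it balanced.

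At stake are precision and an unambiguous primary analysis.

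**Working it through.** **Inputs from the protocol.** 950 patients, about 75 clinicians (950/75 = 12.7 patients each), two-sided alpha 0.05, up to 5% loss; knowledge 44% vs 60% with power above 99%; trust difference 4.1, SD 20, power 86% (all 4.8.3). Allocation is 1:1 (4.8.4).

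**Inputs not in the protocol, so assumed.** ICC 0.02–0.10; 70% pediatric emergency clinicians; clinician-type effect 0–0.5 SD; for the trigger, 5 or 10 independent characteristics each tested at 5%; covariates explaining 10% or 30% of outcome variance.

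**1. The plan's own power figures, without clustering.**
- Knowledge, 475 per arm, treated as a proportion: SE = √[(0.44×0.56 + 0.60×0.40)/475] = 0.0320. Power = Φ(0.16/0.0320 − 1.96) = 99.9%, and 99.8% after 5% loss. The stated figure reproduces.
- Trust: SE = 20×√(2/475) = 1.298. Power = Φ(4.1/1.298 − 1.96) = 88.5%, and 86.9% after 5% loss, in line with the stated 86%.
- With design effect 1 + (12.7 − 1)×ICC, knowledge has 91–99% power over ICC 0.02–0.10. Trust falls to 79–81% at ICC 0.02 and 55–57% at ICC 0.10. Trust therefore has little precision to spare.

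**2. Omitting clinician type.** Take 76 clinicians with 12.5 patients each, type balanced between arms. In SD units the variance of a clinician mean is V = ICC + (1 − ICC)/12.5. Ignoring type adds p(1 − p)d² to the apparent variance, where p is the share of pediatric emergency clinicians and d the type effect. The ratio of reported to correct SE is √[1 + p(1 − p)d²/V].
- ICC 0.02, d = 0.3: V = 0.0984; √(1 + 0.0189/0.0984) = 1.092.
- ICC 0.10, d = 0.2: V = 0.172; √(1 + 0.0084/0.172) = 1.024.

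Simulation of the same design agrees (for these two cases 0.0784/0.0718 = 1.092 and 0.0971/0.0947 = 1.025):

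| Type effect | SE too large by | Type I error, type omitted | Power lost, starting near 80% |
|---|---|---|---|
| 0 | 0% | about 5% | none |
| 0.2 SD | about 3–4% | about 4% | about 2 points |
| 0.3 SD | 5–9% | 3–4% | 4–6 points |
| 0.5 SD | 14–24% | 1.5–2.6% | 9–17 points |

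The share matters too. If p were 90%, p(1 − p) falls from 0.21 to 0.09, and the 9.2% at ICC 0.02 and d = 0.3 falls to √(1 + 0.0081/0.0984) − 1 = 4.0%.

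**3. The imbalance trigger.** The chance that at least one of k independent characteristics differs at 5% under correct randomization is 1 − 0.95^k: 22.6% for k = 5, 40.1% for k = 10.

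A simulation with 950 independent patients (no clustering) compared the strategies:
- Type I error was 3.8–4.4% with triggered adjustment. The two fixed tests in the same runs gave 4.0–4.8%, so the trigger alone shows no inflation.
- Power was about 80–81% with the trigger, hardly better than unadjusted (about 80%). A fixed full model gave 83–84% when covariates explain 10% of variance and 91% when they explain 30%.
- Taking the smallest p-value of the unadjusted, triggered and full models gave type I error of 6.0–6.8%.

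**The case against.** The first sentence of the analysis plan is unconditional: the clustered, site-stratified test will be done. The regression can be read as a supplement, with nothing switching. That reading is open and the wording does not exclude it, but the protocol does not state it, and saying that differences will be accounted for does not sound like a sensitivity analysis. What stands is that a reader should not conclude that the headline result would change in 40% of such trials. That figure assumes ten independent characteristics, a 5% threshold and replacement of the first analysis, none of which the protocol states.

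A reader might also infer that a data-dependent analysis must inflate type I error. The check does not support this. Both the trigger and the omitted stratifier leave the test at or below its nominal level, and inflation needs a choice among results that the protocol does not describe.

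Six of the seven sites in 4.3.1 are named children's hospitals, so clinician type may vary little within site and site may already capture much of it. This stands as a reason why the loss may be small.

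The trigger could be defended as a safeguard, since clinicians are randomized before they treat eligible patients and neither they nor parents are blinded, so recruitment could differ between arms. That is a reason to adjust. A covariate list fixed in advance does so whether or not a difference is noticed.

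Finally, a covariate list is commonly left to the SAP, which is not at hand. That is fair for the list, but not for a conditional rule that the protocol itself states.

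**Conclusion.** The point holds as one of precision and clarity. Adjustment is tied to observed imbalance, the main result is not identified when adjustment is made, and one of two balanced factors is missing from the comparison. If the omitted variables are prognostic, the standard error is too large and the test conservative. The treatment estimate is not biased by this, and a false-positive primary conclusion is not made more likely unless the headline result is chosen after several models are seen.

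Under a clinician-type effect of 0.2–0.3 SD, 70% pediatric emergency clinicians and ICC 0.02–0.10, the SE is about 3–9% too large, costing about 2–6 power points where power is near 80%. If type is not prognostic the cost is zero. All three inputs are assumptions. Knowledge keeps about 91–99% power over that ICC range, so the primary outcome is little affected; trust and similar outcomes have more to lose.

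It is tempting to express the gain from adjustment as a number of extra patients. The documents do not support one: they give no explained variance and no ICC, and patient-level covariates mainly reduce variance within clinicians, so a conversion that ignores clustering would mislead.

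This should be fixed, but the trial's main conclusion does not hang on it.

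**What to change.** In Protocol 4.8.1, and in the SAP to match:
- Delete the rule that makes adjustment conditional on baseline differences.
- Name one primary model per outcome, used whatever the observed balance: arm, site and clinician type, with a clinician random effect.
- Add a short list of prognostic covariates, fixed before outcome data are seen and limited to values that the discussion cannot change. Flag any survey covariate recorded after the discussion (4.6, footnote 4), and reconcile 4.7.1 with 4.8.1 on when education is collected.
- Report the unadjusted clustered comparison as a sensitivity analysis.

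The cost is about a paragraph of wording. No new data are needed and the sample size of 950 does not change.
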